#### Functional near-infrared spectroscopy

fNIRS is a non-invasive and portable neuroimaging technique that uses near-infrared light which penetrates the skull to detect changes in oxygenated haemoglobin (O_2_Hb) and deoxygenated haemoglobin (HHb) concentrations within the cortical microcirculation, such as the capillary, arteriolar and venular beds. fNIRS will be used in conjunction with the Stroop and Go/No-Go tasks to measure task-related changes in DLPFC activation. Task-related changes in fNIRS haemodynamic response activation show adequate to high reliability (ICC = 0.42–0.87) [44] and have been validated against the gold standard functional magnetic resonance imaging (fMRI) blood oxygen level-dependent response [45, 46].

A multi-channel continuous-wave fNIRS system (OxyMon Mk III; Artinis Medical Systems, Elst, The Netherlands) will be used to measure task-related changes in O_2_Hb and HHb concentrations in the left and right DLPFC during the Stroop and Go/No-Go tasks [47, 48]. An eight-channel fNIRS optode montage will be used (four channels on each hemisphere), and each transmitter and receiver optode pair will be placed between 30 mm and 40 mm apart for optimal near-infrared light penetration into the cortical layer.

Oxysoft data acquisition software (Artinis Medical Systems) will be used for fNIRS data collection and analysis. The modified Lambert-Beer law, assuming constant scattering [49], will be adopted to detect concentration changes of O_2_Hb and HHb in the left and right DLPFC, dependent on the changes in detected light intensity. For analysis, O_2_Hb and HHb signals of the four channels of each hemisphere will be averaged. The moving SD based artefact removal method will be used within each trial to remove movement artefacts and other noise from the fNIRS signals [50]. The thresholds for artefact detection will be set to 0.45 for O_2_Hb and 0.18 for HHb [51], with a window length for moving SD calculation at 0.5 seconds, and a window length for artefact correction (LOESS smoothing window) at 1 second. The fNIRS signals will then be linearly de-trended per trial and low-pass-filtered at 0.1 Hz to remove heart rate and other high-frequency physiological signals. To enable direct comparison of the different trials within each task, the filtered signals will be biased using the average concentration of the 5 seconds before the “start” instruction as a reference (zero). Then, individual trials will be averaged per task to create three mean time-course signals per person, which will then be averaged over all participants. Last, the peak and mean concentrations of O_2_Hb and HHb will be calculated over all trials for all participants and then averaged for each of the tasks.

#### Quality of life

The 39-item Parkinson’s Disease Questionnaire (PDQ-39) is a valid and reproducible PD-specific measure of QoL [52, 53]. Each question is based on a 5-point ordinal scoring system ranging from 0 = never to 4 = always. There are eight dimensions, with each dimension score being the sum score of each item in the dimension divided by the maximum possible score of all the items in the dimension, multiplied by 100. The overall score is known as the Parkinson’s disease summary index and is the sum of all dimension total scores divided by 8.

#### Functional assessments

The UPDRS, Mini Balance Evaluation Systems Test (mBEST), Five Times Sit to Stand Test (5TSTST), 10-Metre Walk Test (10MWT), Four Square Step Test (4SST) and maximal lower limb strength (one-repetition maximum [1RM] leg press) will be used to assess disease-related motor function and lower extremity physical function. Each of these tests will be performed in the same order each time with the participants wearing their own footwear and will be conducted by the attending researcher.

Section III of the UPDRS will be used to measure disease-related motor function and has shown excellent reliability (ICC = 0.90) [54]. The UPDRS comprises 33 scores based on 18 questions with several right, left or other body distribution scores.

The mBEST is a reliable tool (ICC = 0.92) [55] that assesses four domains of dynamic balance, including anticipatory postural adjustments, reactive postural control, sensory orientation and dynamic gait. The testing series consists of 14 tests, with each of the 14 items rated on a 3-level ordinal scale (ranging from 0 = cannot perform/severe, to 2 = normal) for a total score of 28 points. For the two items that are assessed bilaterally, the lower score will be used for the composite score. A cut-off score of 20 of 28 will be used to distinguish participants as ‘at risk’ for falls [55].

The 5TSTST will be used to determine functional lower limb power and has excellent test-retest reliability for people with PD (ICC = 0.91) [56]. Participants begin the 5TSTST test sitting in an armless chair with a height of 45 cm [34]. The participants will be instructed to cross their arms over their chest and sit with their back against the upright back-rest of the chair, with their feet placed flat on the floor and their knees at 90 degrees. They will then be instructed to quickly and repeatedly rise to a full standing position and then sit back down on the chair for five repetitions. A single repetition will be defined as a vertical standing position with an upright trunk and with the hips and knees extended. The test will begin once the participant moves off the chair for the first stand and will finish once the participant sits following the fifth sit-to-stand repetition, with the total time to completion recorded in seconds.

The 10MWT will be used to determine gait speed and has shown excellent test-retest reliability for comfortable gait speed (ICC = 0.96) and maximum gait speed (ICC = 0.97) for people with PD [57]. The test is set up with two cones positioned 10 m apart, with two more cones positioned at the 2-m and 8-m marks. The participant is instructed to walk the entire 10 m, but only the time from the moment the participant reaches the 2-m cone to the moment they reach the 8-m cone (distance of 6 m) is recorded to accommodate for acceleration and deceleration periods. Each participant will perform three trials at two different walking speeds: comfortable speed and fast speed. Each trial will be separated by a 1-minute rest period, and each trial will be recorded in seconds. The average speed in metres per second will be calculated and used for analysis [57].

The 4SST will be used to determine dynamic balance and stepping speed in four directions [58]. The 4SST has shown excellent test-retest reliability (ICC = 0.98) for people with PD [59]. Participants will be asked to step forwards, sideways and backwards over two metal rods positioned flat on the floor in a cross formation. The test begins with the participant moving first in a clockwise direction and returning in a counter-clockwise position to the start square. Participants will be asked to step with two feet into each square without touching or stepping on the rods as quickly as possible. A practise trial will be performed first, followed by two true attempts, which will be recorded with a stopwatch. The fastest time of completing the sequence in seconds will be used for analysis.

#### Functional strength of the lower limb

Lower extremity strength will be assessed using a 1RM leg press, which has previously shown excellent test-retest reliability for people with PD (ICC = 0.87–0.98) [60] and will be conducted using fixed pneumatic leg press (Air300; KEISER, Fresno, CA, USA). Ten warm-up repetitions will be performed prior to any near-maximal effort. The participant will then perform a near-maximal repetition (estimated at 80% of their 1RM) while maintaining correct technique, following which the resistance will be incrementally increased by 5–10% as appropriate, until the participant can no longer perform a full repetition [61]. Three minutes’ rest will separate each maximal attempt, and verbal encouragement will be provided. The highest resistance used to perform a successful repetition will be recorded as the 1RM in kilogrammes.

### Additional measures

Height will be measured to the nearest 0.1 cm using a standardised portable stadiometer. Weight will be measured to the nearest 0.1 kg using a standardised set of scales. Both height and weight will then be used to calculate body mass index in kilogrammes per metre squared. To ensure consistency of the data collection, participants will be instructed to wear light-fitting clothes and remove loose items before standing barefoot while having their height and weight recorded. Finally, interviews will be conducted with participants to monitor habitual physical activity and to establish any medication (in addition to PD-related medication) that they may be taking throughout the length of the intervention.

### Exercise compliance

Participants will be required to complete a minimum of 20 of the 24 scheduled training sessions (representing > 85% attendance) within the entirety of the 12-week intervention period. If sessions are missed, participants will be given an opportunity to complete additional sessions to make up for the missed sessions. This completion percentage is typical of large community-based exercise intervention studies and meets standard expectations of per-protocol analysis [62]. Compliance will be recorded using attendance sheets, which will be filled out by the attending researcher after each training session.

### Adverse events

The attending researcher will discuss what an adverse event (AE) is with each participant before the intervention begins. For this trial, an AE will be defined as any unfavourable and unintended sign, symptom or disease temporarily associated with the intervention (either exergaming or a-tDCS), without any understanding about causality or relationship to the therapy. The attending researcher will ask each participant before training begins about any AEs experienced and will document all AEs associated with the intervention. Usual care participants will be phoned and asked fortnightly about any experienced AEs. All AEs will be reported following the guidelines recommended by the National Health and Medical Research Council position statement (https://www.nhmrc.gov.au/guidelines-publications/e112). All participants will be asked to contact the attending researcher immediately after experiencing an AE, which will be recorded and promptly reported to the chief investigator, who will then determine its seriousness and causality in conjunction with any medical staff attending the event. Any AEs that are related to any part of the intervention will be reported to the Deakin University Human Research Ethics Committee.

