### Intervention

The training intervention will be conducted over a 12-week period and will consist of exergames using an augmentative virtual reality software (Jintronix, Montreal, QC, Canada) with concurrent a-tDCS. Participants will be required to attend training sessions at Deakin University, Burwood campus, twice per week on non-consecutive days (24 training sessions in total). The exergaming training sessions will be supervised by the attending researcher and will last approximately 30 minutes. Jintronix rehabilitation software, which contains over 100 rehabilitation exergames, along with a three-dimensional motion capture sensor (Kinect®), will be used in this study. The exergames performed by the participants will be pre-selected by the attending researcher and tailored to each participant’s physical needs. The participant’s programmes will include exercises that focus on multiple domains of balance, including bilateral weight transfer, unilateral balance ability, trunk mobility and transitional activities (e.g., standing from a chair). An example balance training programme is illustrated in Fig. 2.

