### Trial status

Eighteen participants have completed 24 weeks of training and are waiting to be tested at 3-month follow-up. No dropouts or adverse events have been reported.

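### The AE definition does not fit usual care and AE enquiry is scheduled differently there, so exergaming-versus-usual-care AE counts carry ascertainment bias; real versus sham does not

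*Protocol article*

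**What the plan says.** All the rules are in the protocol article, Adverse events, except the training schedule, which is under Intervention.

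- **Definition.** An AE is an unfavourable, unintended sign, symptom or disease "temporarily associated with the intervention (either exergaming or a-tDCS"; the sentence then sets causality aside.
- **Exergaming arms, real and sham.** The attending researcher "will ask each participant before training begins about any AEs experienced and will document all AEs associated with the intervention".
- **Usual care.** "Usual care participants will be phoned and asked fortnightly about any experienced AEs".
- **All arms.** "All participants will be asked to contact the attending researcher immediately after experiencing an AE". Such a report is recorded and passed to the chief investigator, who then judges seriousness and causality.
- **Training schedule.** Sessions take place "twice per week on non-consecutive days (24 training sessions in total", over 12 weeks. Follow-up then runs to week 24.

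**The concern.** Two separate features push in the same direction during the first 12 weeks.

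First, the definition names an exposure that one arm does not have. A usual care participant has no exergaming or a-tDCS for an event to be associated with, even in time only, yet the same section has these participants phoned about AEs. The section does not say what would count as an AE in that arm. The link to the intervention appears again in the instruction on what to document.

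Second, the exergaming arms are asked more often, and face to face. Minor events are forgotten, so more frequent asking finds more of them at the same true rate.

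What is at stake is any statement on the safety of exergaming relative to usual care, and the counting of falls. Every participant must have fallen in the previous 12 months (Telephone screening), and fall reduction is part of the trial's rationale (Background, Discussion). Falls are not among the outcome measures that the article describes, so AE reporting is the only route in the text by which a fall would be counted. It is unclear whether a fall at home meets a definition framed as a sign, symptom or disease linked to the intervention.

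**Working it through.** **Inputs.** Two sessions a week for 12 weeks, stated total 24 (Intervention); minimum attendance 20 (Exercise compliance); fortnightly calls in usual care (Adverse events); 24 weeks in all, the last 12 after the intervention (Methods/design); 8 participants per arm (Sample size calculation).

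**Reproducing the stated figure.** 2 × 12 = 24 sessions, as the article says.

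**Scheduled enquiries per participant, weeks 1 to 12.**
- Each exergaming arm: 24, or 20 at minimum attendance.
- Usual care: 12 / 2 = 6.
- Exergaming to usual care: 24 / 6 = 4.0, or 20 / 6 = 3.3.
- Real to sham: 24 / 24 = 1.0.

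The counts of 24 and 20 assume a question at every session. The text says "The attending researcher will ask each participant before training begins about any AEs experienced", without specifying each session. That is the natural reading, because explaining AEs before the whole intervention has its own sentence.

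**Weeks 13 to 24.** No enquiry is described for the exergaming arms, so 0. For usual care it is 12 / 2 = 6 if the calls continue; the article does not say when they stop. If they do continue, the imbalance reverses in this period, and over 24 weeks the totals are 24 against 6 + 6 = 12. The overall ratio of 2:1 would then hide two imbalances in opposite directions.

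**What unequal asking could do to counts (illustration; recall rates are assumed, not taken from the documents).** Suppose the chance of recalling a minor event decays exponentially with half-life h days, and events are found only at scheduled enquiries. The share captured with an interval of L days is (1 − exp(−kL)) / (kL), with k = ln 2 / h. Twice-weekly asking gives L = 3.5; fortnightly asking gives L = 14.

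| h (days) | L = 3.5 | L = 14 | ratio |
|---|---|---|---|
| 3 | 0.686 | 0.297 | 2.31 |
| 7 | 0.845 | 0.541 | 1.56 |
| 14 | 0.918 | 0.721 | 1.27 |
| 28 | 0.958 | 0.845 | 1.13 |

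At equal true rates, the exergaming arms could thus show about 1.1 to 2.3 times as many minor events as usual care. Memorable events would sit at the low end. Immediate reporting would shrink the ratio; a definition that filters out control events would enlarge it.

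**The case against.** The strongest reply is that the safety contrast that isolates a-tDCS is sound. Real and sham participants have the same definition, questions, visits and attending researcher, and researcher and participant are both blinded to the stimulation code (Allocation and blinding). This stands in full. A reader might infer that no between-arm safety statement is possible; the document does not support that.

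Second, the definition sets causality aside, so it describes association in time (*temporally* is probably the intended word) rather than attribution. Controls are asked about AEs, and every participant is told to report one at once. This also stands. A reader might infer that control counts are zero by definition, but the section plainly means to record events in that arm. The drafting is contradictory rather than exclusionary. It is only a partial rescue, because the AE concept explained to participants is presumably the one in the same section.

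Third, the gap after week 12 is silence in a condensed article, and every arm is assessed at week 24. This is fair. The point is limited to no scheduled enquiry being described, while one is described for usual care with no stated end.

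Fourth, the trial is exploratory, has 8 per arm and states no safety hypothesis. Closer questioning of treated participants is ordinary monitoring, and in weeks 1 to 12 its bias runs against the intervention. That limits the weight of the point but does not make the exergaming and usual care counts comparable.

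Finally, the Trial status section says of 18 participants: "No dropouts or adverse events have been reported". A reader might take this as proof that falls are being missed. The document gives no rate of falls per person from which to judge it, the exposure time described there is unclear, and general under-reporting would not show a difference between arms. It is not relied on here.

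**Conclusion.** The point holds for exergaming against usual care. The AE definition refers to an exposure that controls lack, and scheduled enquiry differs by about 4:1 in the first 12 weeks (3.3:1 at minimum attendance) and in mode. Counts compared across these arms are biased by ascertainment, though not uninterpretable, because all arms share the instruction to report immediately. The 4:1 figure rests on reading the pre-training question as asked at each session; a reversal after week 12 rests on the calls continuing. The size of the effect on counts cannot be derived from the document.

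The point does not extend to real against sham, where ascertainment is equal. Those arms share only the incomplete capture after week 12. The primary outcome is unaffected. The wording and schedule should be changed, because this is cheap and falls have no other route into the data in the text.

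**What to change.** 1. Define an AE in all three arms as any untoward event, including any fall, from randomisation to week 24, whatever its cause. Keep the causality judgement as a separate, later step, as the section already does.
2. Put the same scripted enquiry to every arm each fortnight to week 24, covering the whole preceding fortnight including anything already mentioned. In weeks 1 to 12 the exergaming arms can answer it at a training visit; afterwards it is a call. A difference in mode during training then remains, unless the telephone is used throughout.
3. Base any exergaming-versus-control comparison on those enquiries only. List events elicited at additional training visits separately.
4. For participants already past these visits, disclose the unequal ascertainment and qualify the comparison.

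After the change every arm has 6 enquiries in 12 weeks and 12 in 24 weeks, a ratio of 1:1.

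The cost is the wording, plus about six short calls per exergaming participant in weeks 13 to 24: at most 16 × 6 = 96 calls if all 16 were still to be followed, and fewer now, since some have already passed this stage. The AE listing will be longer, because unrelated events and falls will appear in it.

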### Sample size calculation

On the basis of data provided by Shih et al. [31], whose primary outcome was the LOS to assess reaction time and excursion endpoints in people with PD (Cohen’s *d* = 0.74, 77% improvement in reaction time, 89% improvement in endpoint excursion), a sample size calculation using G*Power statistical software estimated a sample size of five participants per group would be sufficient for 85% power (α = 0.05) while using a conservative estimated SD change of ± 5. It is difficult to determine if this is a large-enough sample size to detect change between the real and sham a-tDCS conditions, given the paucity of literature using a testing paradigm of exercise + real a-tDCS vs exercise + sham a-tDCS vs control. However, using the percentage changes between real and sham conditions reported by Kaski et al. [28], we postulate that a sample size of 18 participants will be enough to detect a medium effect size between the real and sham a-tDCS groups (Cohen’s *d* = 0.5) with an estimated SD change of ± 25 for the retropulsion pull test. The LOS and SOT measures were not used by Kaski et al. [28]; therefore, the retropulsion pull test was selected because it contains a balance perturbation similar to that of the SOT. Therefore, to accommodate for a 20% dropout rate, we aim to recruit 8 participants per group (24 participants in total).

### Statistical analysis

Statistical analyses will be conducted using Stata version 11 statistical software (StataCorp, College Station, TX, USA). A generalised linear mixed model with factors for time (0, 6, 12 and 24 weeks), group (exergaming + sham a-tDCS vs exergaming + real a-tDCS vs control) and group-by-time interaction will be used to determine the effect that different direct current stimulation interventions have on brain excitability and balance. Potential factors such as the participant’s age and time since diagnosis will be used as covariates for analyses within our models. Per-protocol analysis will also be performed by including all participants who are at least 85% compliant with the exercise (as measured by the number of exercise sessions attended). Post hoc analyses using the Bonferroni correction will be applied as appropriate. Pearson’s product-moment correlation coefficient will be used to measure the level of correlation between change scores of the functional tests and brain excitability and activation. Significance will be set at *P* < 0.05.

When possible, we will try to obtain all endpoint measures from any dropouts in the final analysis. For participants who are lost to follow-up, missing data will be handled using the multiple imputation method [63]. Because the multiple imputation method assumes only that data are missing at random [64], we will additionally perform sensitivity analyses to evaluate the potential effect of non-random attrition [65]. Sensitivity analyses will involve testing a range of plausible scenarios in outcomes for participants who were lost during follow-up [66].

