In our study, exergames are used to deliver cognitive and static and dynamic balance exercises for people with PD. The Jintronix software used in our study is capable of using an inexpensive, commercially available motion capture camera to deliver a vast selection of rehabilitation games from a personal computer or laptop. Additionally, the use of a-tDCS to augment adaptive neuroplasticity may lead to greater and longer-lasting improvements in balance and lower limb function in people with PD. Thus, we hypothesise that (1) balance will improve for the exergaming groups compared with controls and (2) the addition of real a-tDCS will provide additive improvements. Novel home care therapies that are easily administered are likely to maintain exercise enjoyment and facilitate long-term exercise adherence. Therefore, if this trial is successful, this intervention will potentially allow for a high degree of scalability into a community- or home-based setting, where exergames can be implemented either as part of a rehabilitation programme in health-care facilities (i.e., rehabilitation hospitals, age care facilities and nursing homes) or as an adjunctive therapy that can be performed at home in conjunction with standard therapy. Our study also has the potential to have wider implications for reducing total health-care costs (i.e., hospitalisation, injury management and assistive care costs) associated with falls for people with PD.

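### Bonferroni-corrected post hoc contrasts are the only stated route to the pairwise hypotheses; the sample size makes no allowance for them, and with three arms a gated test would avoid much of the power loss

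*Protocol article*

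**What the plan says.** **Hypotheses.** The Discussion expects the exergaming groups to improve relative to control and then, as its second hypothesis, "2) the addition of real a-tDCS will provide additive improvements". The second is a real-versus-sham comparison.

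**Analysis.** The Statistical analysis section specifies a generalised linear mixed model with group (three levels), time (0, 6, 12 and 24 weeks) and their interaction. It sets significance at P < 0.05. For follow-up contrasts it says "Post hoc analyses using the Bonferroni correction will be applied as appropriate". It does not list the contrasts, give the number corrected for, or require a significant overall test first.

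**Sizing.** The Sample size calculation says of its first step that "a sample size of five participants per group would be sufficient for 85% power (α = 0.05" on the stated d of 0.74. For the tDCS question it then says that "a sample size of 18 participants will be enough to detect a medium effect size between the real and sham a-tDCS groups", with d = 0.5 but no alpha or power. After 20% dropout the target is 8 per group, 24 in total.

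**The concern.** A three-level group factor and its interaction do not by themselves answer a question about two particular arms. Each pairwise hypothesis therefore needs a follow-up contrast, and Bonferroni is the only rule given for those. That has two consequences.

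- The sample size justification and the analysis do not match: a sizing step run at 0.05 with no multiplicity allowance does not describe the power of a contrast tested at a smaller alpha.
- The penalty falls on a very small trial. At 8 per arm, dividing alpha by three roughly halves the power for the effect sizes that the protocol itself quotes. In a three-arm trial, family-wise error over arms can be controlled at lower cost.

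**Working it through.** **Inputs.** Three arms, 8 per arm, d = 0.74 (first step), d = 0.5 (real versus sham), alpha 0.05 and 85% power (first step): Sample size calculation. Three groups, three post-baseline visits, Bonferroni: Statistical analysis. Assumed here: two-sided tests, a normal outcome, equal SDs, one change score per participant, and no gain from covariates or repeated measures.

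**1. The plan's own figure.** For a two-sample t-test the noncentrality is δ = d√(n/2) on 2n − 2 degrees of freedom. With d = 0.74 and n = 5, δ = 0.74 × √2.5 = 1.17, the critical t on 8 df is 2.306, and power is 18%, not 85%. That test would need 34 per arm. A 3 × 4 repeated-measures interaction with f = d/2 = 0.37 and an assumed correlation of 0.5 gives 81% with 15 participants in total. So the stated figure does not show which test its alpha of 0.05 belongs to.

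**2. Per-comparison alpha (family inferred).** Three arm pairs: 0.05/3 = 0.0167. Three pairs at three post-baseline visits: 0.05/9 = 0.0056.

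**3. Pairwise power at 8 per arm.** √(8/2) = 2, so δ = 2d: 1.00 at d = 0.5 and 1.48 at d = 0.74. Critical t on 14 df is 2.145, 2.718 and 3.273 at the three alphas.

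| d | 0.05 | 0.0167 | 0.0056 |
|---|---|---|---|
| 0.5 | 15.4% | 6.8% | 2.9% |
| 0.74 | 28.1% | 14.45% | 6.9% |

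The loss depends on the effect. If 5 per arm truly gave 85% at 0.05, d would be about 2.17, and 8 per arm would fall only from 98% to 93%.

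**4. Why a gate is enough with three arms.** Take a 2-df test of equality at 0.05, followed by pairwise tests at 0.05 only if it rejects.

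- If all three arms are equal, any false claim needs a false rejection at the gate, which has probability at most 0.05.
- If exactly one pair is equal, there is only one true null pair, and it is tested at 0.05.
- There is no other case containing a true null pair.

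**5. Simulation** (three arms of 8, one time point, error variance pooled over the arms, 200,000 runs).

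| Procedure | Family-wise error, all arms equal | One arm far from the other two |
|---|---|---|
| Unadjusted pairs, no gate | 11.8% | about 5% |
| Gate, then pairs at 0.05 | 5.0% | about 5% |
| Bonferroni, no gate | 4.2% | 1.7% |

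Real-versus-sham power:

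| Real − sham | Sham − control | Gated | Bonferroni |
|---|---|---|---|
| 0.5 SD | 0 | 10% | 7% |
| 0.5 SD | 0.5 SD | 13% | 7% |
| 0.5 SD | 0.74 SD | 15% | 7% |
| 1.0 SD | 0 | 39% | 30% |
| 1.0 SD | 1.0 SD | 48% | 30% |

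With this pooled error, Bonferroni rejects a pair that the gated test misses in under 0.3% of runs. The 1.0 SD rows illustrate a larger effect; the protocol does not give that value.

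**The case against.** **Bonferroni is standard, valid and protective.** This stands. The plan writes no gate, and against ungated unadjusted pairs Bonferroni cuts family-wise error from 11.8% to 4.2%. A reader might infer that the correction buys nothing; that is true only relative to a gated procedure that the plan does not contain.

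**The thresholds are not in the document.** This also stands. No family is stated, and a condensed article may leave it to a statistical analysis plan. The values 0.0167 and 0.0056 are conditional, and the missing family is not itself the point. The point is that the method named costs power, and that the sizing shown makes no allowance for it.

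**A P < 0.05 rule and Bonferroni do not conflict.** Correct. A reader might infer that a real-versus-sham p between 0.0167 and 0.05 succeeds under one sentence and fails under another. But Bonferroni-adjusted p-values compared with 0.05 are coherent, and a sizing alpha is not a decision rule.

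**Alpha 0.05 is not tied to real versus sham.** Correct. It belongs to the five-per-group step, which may concern an overall or interaction test. The real-versus-sham step states no alpha, so a direct mismatch for that contrast cannot be shown; only the absence of any allowance can.

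**The three-arm argument fails over several visits.** It does if the visits go uncorrected: with one arm clearly different, testing the remaining null pair at weeks 6, 12 and 24 without correction gives 11–13% error (assumed between-visit correlation 0.5–0.7). The gate must therefore apply at a given visit, with a separate correction across visits.

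**The trial calls itself exploratory.** That lowers the consequence. It still states directional hypotheses, a power target and a significance level.

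**Conclusion.** The point holds in a limited form. The only stated route to the pairwise hypotheses is a Bonferroni-corrected contrast, and the sample size section makes no allowance for it. If the family is the three arm pairs, power at 8 per arm roughly halves: 15% to 7% at d = 0.5 and 28% to 14% at d = 0.74. A gated three-arm test at a given visit keeps family-wise error at 0.05 and recovers part of the loss: 10–15% against 7% at d = 0.5, and 39–48% against 30% at 1.0 SD.

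These figures rest on a simple change-score comparison. Baseline adjustment or repeated measures could raise them all, but the protocol gives no correlation from which to say by how much.

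A reader might also infer that the change would make the tDCS comparison adequately powered. It would not: at d = 0.5 even an uncorrected test has 15% power, and 80% needs 64 per arm. That is a separate and larger weakness of the sizing.

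**What to change.** 1. **Statistical analysis.** Replace Bonferroni over arms with a gated test. At a given visit, test with 2 df at 0.05 that change from baseline is equal in all three arms; only if this rejects, test real versus sham, real versus control and sham versus control, each at 0.05.
2. **Visits and LOS measures.** Wherever more than one visit or LOS measure is tested, keep a separate correction. For example, splitting alpha over weeks 6, 12 and 24 would run the gate and its pairs at 0.05/3 = 0.0167 at each visit.
3. **Sample size calculation.** State the alpha that matches this procedure, including for the real-versus-sham step. If Bonferroni over three pairs is kept, restate pairwise power at 0.0167. On the two-sample t-test the requirement then rises from 64 to 86 per arm for d = 0.5 at 80% power, and from 34 to 45 for d = 0.74 at 85%.

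The cost is a few sentences and no extra data. The downside is that every pairwise claim depends on the three-arm test rejecting first, and simultaneous confidence intervals are less direct than under Bonferroni. Participants had already completed training when the article appeared, so the change should be dated and made before any comparison by arm is seen.
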